## Abstract

**Background:**

Early diagnosis and treatment of the newborn infant with suspected sepsis are essential to prevent severe and life threatening complications. Diagnosis of neonatal sepsis is difficult because of the variable and nonspecific clinical presentation. Therefore, many newborns with nonspecific symptoms are started on antibiotic treatment before the presence of sepsis has been proven. With our recently published single-centre intervention study we were able to show that Procalcitonin determinations allowed to shorten the duration of antibiotic therapy in newborns with suspected early-onset sepsis.

**Methods/Design:**

The study is designed as randomized controlled international multicenter intervention trial on the efficacy and safety of Procalcitonin guided treatment. Term and near-term infants (gestational age ≥ 34 0/7 weeks) with suspected sepsis in the first 3 days of life requiring empiric antibiotic therapy will be included. The duration of antibiotic therapy in the standard group is based on the attending physician's assessment of the likelihood of infection (infection unlikely, possible, probable or proven). In the Procalcitonin group, if infection is considered to be unlikely or possible, antibiotic therapy is discontinued when two consecutive Procalcitonin values are within the normal range. Co-primary outcome measures are the duration of antibiotic therapy (superiority aspect of the trial) and the proportion of infants with a recurrence of infection requiring additional courses of antibiotic therapy and/or death in the first month of life (safety of study intervention, non-inferiority aspect of the trial). The number of infants to be included equals 800 per arm. With these numbers the power of the study to demonstrate superiority for duration of antibiotic therapy as well as non-inferiority regarding safety, i.e. excluding a disadvantage difference larger than 2% for the experimental arm, will both be greater than 80%.

**Discussion:**

Benefit of the study is a possible limitation of unnecessary use of antibiotics. The results of our first study suggest that there is a low risk on discontinuing antibiotic treatment too early, resulting in the development of a neonatal infection with its morbidity and mortality.

**Trial registration:**

This trial is registered in the U.S. National Institutes of Health's register, located at http://www.clinicaltrials.gov. (NCT00854932).

## Background

Infections are the single largest cause of neonatal deaths globally [1]. Based on the onset, neonatal sepsis is classified into two major categories: early onset sepsis, which usually presents with respiratory distress within 72 hours of age and late onset sepsis that usually presents with septicemia after 72 hours of age. Sepsis in neonates is a significant contributor to morbidity and death, with mortality rates varying from 3% to as high as 50% in some series, especially with gram-negative pathogens [2-6]. The incidence of early-onset sepsis in term neonates in The Netherlands 2003-2006 is approximately 0.6% [7].

Early diagnosis and treatment of the newborn infant with suspected sepsis are essential to prevent severe and life threatening complications. In contrast to the clear and valuable therapeutic options, the diagnosis of suspected early-onset neonatal sepsis is challenging. The early signs of sepsis in the newborn are non-specific. Therefore, many newborns with nonspecific symptoms undergo diagnostic studies and the initiation of treatment before the presence of sepsis has been proven. Blood culture is currently the gold standard for the diagnosis of sepsis. However, in addition to the fact that culture reports are available only after 48-72 hours, blood cultures are frequently false negative due to the small amount of blood that can be drawn from neonates [8]. The reliability of most laboratory markers, including white blood cell count (WBC), C-reactive protein (CRP), Procalcitonin (PCT) and IL-6 for the diagnosis of neonatal infection has been assessed in highly diverse groups of ill neonates with a mixture of diagnoses and conditions and has yielded variable results [9]. If culture results come back negative after 48-72 hours, the clinician has to decide whether to provide continued treatment.

In the era of multidrug resistance, it is mandatory to avoid unnecessary use of antibiotics to treat non-infected infants. In addition, the intravenously administration of antibiotics necessitates admission of the neonate to the hospital and thereby separation of mother and child in this delicate period of life. Thus rapid diagnostic test(s) that differentiate infected from non-infected infants, particularly in the early newborn period, have the potential to make a significant impact on neonatal care. In an effort to reduce the use of antimicrobial agents in neonates, clinical studies have been undertaken using the biomarker CRP to safely influence the length of antimicrobial therapy [10,11]. Thus far, no evidence has been presented that using CRP can make an impact on the length of antimicrobial therapy.

Another biomarker that has been discovered more recently, PCT, is proven to be a good marker of severe, invasive bacterial infections in children. All studies on severe, invasive bacterial infections in children report higher sensitivities and specificities of PCT than for CRP [12-16]. PCT is a 116-aminoacid peptide and one of the precursors of calcitonin. The physiological function of calcitonin remains unknown. No disorders attributable to either an excess or a deficiency of calcitonin have been identified. Most microbial infections induce a ubiquitous increase in CALC1 gene expression and a subsequent release of calcitonin precursors from all tissues and cell types throughout the body [17]. In bacterial infections, PCT increases from concentrations in the picogram range (below the detection level of current PCT assays) to plasma concentrations ranging from 1 to 1000 ng/ml. This increase often correlates with the severity of the disease and with mortality [18-21]. Increases in PCT occur more rapidly than increases in CRP. PCT can be detected in the plasma 2 hours after the injection of endotoxins. Within 6-8 hours, PCT concentrations rise and a plateau is reached after approximately 12 hours [22]. CRP can be detected in the plasma after 12 h and reaches a plateau after 20-72 hours. PCT and CRP decrease to their normal values after 2-3 days and 3-7 days, respectively [23-25].

The use of PCT as a marker of neonatal bacterial infection is complicated by several factors. First, infants with respiratory distress syndrome, hemodynamic failure, perinatal asphyxia, intracranial hemorrhage, pneumothorax, or after resuscitation have raised serum PCT concentrations that do not differ from those of septic neonates up to 48 h after onset of clinical signs of distress or infection [26-28]. Second, a physiological increase of PCT has been reported up to 48 h post partum [29]. Third, prepartum and intrapartum administration of antibiotics may affect PCT concentrations in the umbilical cord [30], and postnatal administration of antibiotics will decrease PCT concentrations more rapidly than CRP concentrations [31,32]. When these pitfalls are taken into account, PCT performs better than CRP in diagnosing neonatal bacterial infection.

Chiesa et al developed a nomogram for PCT [33] and Assumma and colleagues performed a longitudinal study on PCT values in healthy neonates [34]. In his findings Chiesa was able to report two major differences in between healthy and septic neonates which formed the basis of his nomogram. Firstly, the level of elevation in PCT was much higher in septic neonates versus healthy newborns and secondly, the absence of a decrease of PCT values after the initial cytokine release post-partum is indicative of a bacterial infection. With all PCT values being increased during the first two days of life, a reference range covering this time period with intervals of several hours is a tool to identify septic neonates. The adult reference ranges apply from three days after birth. Using PCT in this manner has been proven extensively to be a very reliable marker for the diagnosis of neonatal sepsis [35-39].

In recent years a novel indication for the use of PCT has been discovered, related to its described high negative value. It has been reported in many interventional trials [40-44] that a low PCT indicates the absence of a need for antimicrobial therapy. In several countries the recent adult intensive care guidelines have been altered to the extent that PCT has displaced CRP in the recommendations [45,46]. Applying this principle to neonatology, we performed a single-centre intervention trial in Lucerne, Switzerland that showed that serial PCT determinations allowed to shorten the duration of antibiotic therapy in term and near-term infants with suspected early-onset sepsis [47]. This study is designed to test the reliability of a PCT-based strategy in a larger cohort of neonates.

## Methods/Design

The purpose of this trial is to evaluate whether PCT measurements are able to reduce antibiotic usage in suspected neonatal early-onset sepsis by reducing the duration of antibiotic treatment with unchanged outcome. The study is designed as randomized open controlled international multicenter intervention trial on the efficacy (superiority aspect) and safety (non-inferiority aspect) of PCT guided treatment.

### Outcome measures

Co-primary outcome measures are the duration of antibiotic therapy and the proportion of infants with a recurrence of infection requiring additional courses of antibiotic therapy (within 72 hours after ending antibiotic therapy) and/or death in the first month of life (safety of study intervention). A secondary outcome measure is the length of hospitalisation stay.

### Inclusion/Exclusion criteria

Inclusion criteria: Term and near-term infants with a gestational age ≥ 34 0/7 weeks, age 0-3 days of life, suspected sepsis in the first 3 days requiring empiric antibiotic therapy, parental consent. Exclusion criteria are severe congenital malformations and surgical procedures before or during the study. In case of surgical procedures during this trial patients will be excluded from the study and its analyses. These children will be treated by current protocols of care, including protocols for antibiotic therapy. Patients are not allowed to enter the trial for a 2^nd ^time.

Patients will be randomized between t = 0 and t = 12 h after the initiation of antibiotic treatment. Part of the neonates will be eligible for inclusion immediately after birth. Since it is not always possible to ask informed consent from parents immediately after a child is born, this timeframe for randomization of 12 hours is necessary. Randomization will be to either a standard treatment based on conventional laboratory parameters (standard group) or to PCT-guided treatment (PCT group) blocked by centre: Randomization is done by drawing group assignment cards in opaque sealed envelopes (Switzerland) and by computer based digital randomization (The Netherlands).

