### Statistical analyses

This trial is designed to exclude a difference in the rates of re-infection or death greater than 2% (non-inferiority aspect of the trial). Assuming a 2% reinfection/death rate in each group, 770 patients are required per arm for a power of 80% at one-sided alpha of 0.025. Based on our data of the study in Lucerne [47], with this number of patients a difference between mean antibiotic therapy durations of 10 hours can be detected at two-sided alpha of 0.05 with a power of 95% (superiority aspect of the trial). To allow for some unevaluable cases 800 per group will be included.

Primary analyses: The two-sided 95% confidence interval for the difference (experimental - control) in re-infection/death rates will be calculated for the total randomized arms and if this difference excludes +2%, non-inferiority is considered to be shown [48]. Comparison of durations of antibiotic therapy will be done using the Mann-Whitney test with stratification by centre. Any patients dying will be considered as the worst outcome in this evaluation and their duration will be set at the highest duration found. All analyses will be done according to the intention-to-treat principle and will be done with stratification by centre. A per-protocol analysis, excluding patients with major protocol violations, will also be done.

Secondary analysis: Exploratory analysis of primary endpoints regarding the relations with and clinical outcomes assessed at T = 24-72 h will be done using logistic regression or Anova. In the Anova the duration's antibiotic treatment will be transformed logarithmically. All tests are two-sided and p = 0.05 is the limit of significance. These analyses will be informal only because it cannot be excluded that the ratings of clinical outcomes at T = 24-72 h are influenced by the PCT results in the PCT-group. In a secondary analysis reinfection/deaths rates will be compared between treatment arms using random effects logistic regression allowing for centre as a random factor.

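### Infants operated on after randomisation are removed from all analyses, which contradicts intention-to-treat and can take events out of the safety co-primary

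*Protocol article*

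**What the plan says.** The Inclusion/Exclusion criteria section lists surgery as an exclusion both before and after entry: "Exclusion criteria are severe congenital malformations and surgical procedures before or during the study". It then spells out the consequence: "In case of surgical procedures during this trial patients will be excluded from the study and its analyses". On management it adds: "These children will be treated by current protocols of care, including protocols for antibiotic therapy". The same section gives the time of allocation: "Patients will be randomized between t = 0 and t = 12 h after the initiation of antibiotic treatment".

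The Statistical analyses section defines the analysis set differently. The 95% confidence interval for the difference "in re-infection/death rates will be calculated for the total randomized arms", and "All analyses will be done according to the intention-to-treat principle and will be done with stratification by centre". Exclusions appear in that section only for a separate, additional analysis: "A per-protocol analysis, excluding patients with major protocol violations, will also be done".

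The Outcome measures section defines the safety co-primary as recurrence of infection requiring further antibiotics within 72 hours of stopping, and/or death in the first month of life.

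**The concern.** Eligibility is settled at randomisation. Surgery after that point is part of the infant's course, and may depend on how ill the infant is and possibly on the arm. Removing infants because of it breaks the comparison that randomisation set up. It also contradicts the stated analysis principle, so two analysts following this article could build different primary analysis sets.

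The safety co-primary is the most exposed. If stopping antibiotics early led to complications that needed surgery, a later death or recurrence in that infant would leave the PCT arm by rule, and non-inferiority would be easier to show. The trial is open-label, so equal removal from both arms cannot be assumed. The article does not say when the trial period ends for this purpose. Because follow-up runs to a one-month interview, the exclusion could reach surgery that takes place after antibiotics were stopped.

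The duration co-primary is affected too. Deaths are to be given the longest duration observed, and an excluded death loses that penalty.

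**Working it through.** **The two rules side by side.** Take an infant randomised 6 hours after antibiotics start, operated on at day 5, who dies at day 12.
- Under Statistical analyses, the infant belongs to the randomised arm and counts as an event.
- Under Inclusion/Exclusion criteria, the infant is outside the analyses and does not count.

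No text confines the surgical exclusion to the per-protocol set, keeps these infants in outcome follow-up, or plans a sensitivity analysis that includes them. The contradiction needs no arithmetic. The figures below show how much can depend on a few infants.

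**Inputs (Statistical analyses section).** Event rate 2% in each arm, margin 2 percentage points, one-sided alpha 0.025, power 80%, 770 per arm raised to 800 for unevaluable cases.

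**Reproducing the plan's sample size.** n = (1.960 + 0.842)² × 2 × 0.02 × 0.98 / 0.02² = 769.2, rounded up to 770 per arm. This matches.

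**Loss of numbers is not the problem.** By the same normal approximation, power is 81.5% with 800 analysed per arm, 80.0% with 770 and 79.5% with 760 (5% excluded). The allowance from 770 to 800 covers lost numbers. It does not cover selective removal.

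**Sensitivity of the verdict.** Expected events per arm are 0.02 × 800 = 16. One event shifts the difference by about 1/800 = 0.125 points. The Wald upper limit is d + 1.96 × √[p₁(1−p₁)/n₁ + p₀(1−p₀)/n₀], with 16/800 in the control arm:

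| PCT arm | Difference | SE | Upper limit | Non-inferiority |
|---|---|---|---|---|
| 20/800 | 0.500% | 0.741% | 1.95% | shown |
| 21/800 | 0.625% | 0.751% | 2.10% | not shown |
| 20/799 (one event removed from 21/800) | 0.503% | 0.742% | 1.96% | shown |
| 24/800 | 1.000% | 0.780% | 2.53% | not shown |
| 20/796 (four events removed from 24/800) | 0.513% | 0.743% | 1.97% | shown |

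The choice of interval moves the tipping point by one event. With Newcombe or score limits, 19 against 16 passes (1.89%) and 20 against 16 fails (2.03% and 2.04%).

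**Effect on false non-inferiority (illustration only).** The article gives no surgery rate. Assume true rates of 2% in control and 4% in PCT, which is exactly at the margin, and assume that the exclusion removes only infants with events and only from the PCT arm. If a fraction r of that arm is removed, its analysed rate becomes (0.04 − r)/(1 − r) on 800(1 − r) infants.

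| Removed from PCT arm | Analysed PCT rate | Chance of declaring non-inferiority |
|---|---|---|
| 0 | 4.00% | 2.5% |
| 2 infants (0.25%) | 3.76% | 4.7% |
| 4 infants (0.5%) | 3.52% | 8.5% |
| 8 infants (1.0%) | 3.03% | 23% |

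**The case against.** The strongest case accepts that the wording conflicts but disputes how much follows from it.

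- **The harm pathway is conjecture.** The article links surgery neither to infection nor to early stopping, and gives no surgery rate. A natural reading is that surgery is excluded because it disrupts the antibiotic strategy. This stands as a limit on size. It does not justify removing randomised infants from the analysis.
- **The arm-dependent route is narrow.** The arms differ in planned duration only for the unlikely and possible infection categories, and surgery while antibiotics are still running cannot result from stopping them early. This also stands. The route needs surgery after stopping in an infant rated low or intermediate risk, followed by an event.
- **The reversal is a knife-edge.** With the Wald rule, removing one PCT-arm event flips the verdict in about 5% of trials at true rates of 2% v 2%, 6% at 3% v 2% and 1% at 4% v 2%. For four events the figures are about 14%, 26% and 8%. This is fair: reversal is possible, not likely.
- **Retention can also bias.** Operated infants move to usual care, so keeping them may dilute a true difference and favour non-inferiority. This is true of any intention-to-treat non-inferiority analysis, and is a reason to report the planned per-protocol analysis beside it.
- **Serious adverse events are still reported** to the monitoring board. That protects oversight, but does not restore the events to the primary comparison.
- **Perioperative antibiotics might be counted as recurrences.** The Follow up section defines recurrence as a new infection within 72 hours of stopping, so a perioperative course without a new infection does not meet that definition.

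**Conclusion.** The concern holds. The article states two incompatible rules for who enters the primary analyses, and one of them removes infants because of an event after randomisation. This is an error in the text as written, not detail left to an analysis plan: such a plan would have to overrule one of the two statements.

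The contradiction is certain; the size of any bias is not. If surgery is rare and equally frequent in both arms, the effect is small. With about 16 expected events per arm, one excluded event can turn a result just beyond the margin into a pass (2.10% to 1.96% by Wald). In the assumed worst case, where only PCT-arm events are lost, removing 2 to 8 infants raises the false non-inferiority risk from 2.5% to between 4.7% and 23%. These figures rest on the planned 2% control rate, 800 per arm, Wald limits or the matching normal approximation, and one-sided removal. It should be corrected because it decides who is counted in the primary safety test.

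**What to change.** Reconcile the two sections as follows.

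1. Restrict the surgical exclusion criterion to surgery performed before randomisation or already planned at that time.
2. State that infants operated on later stay in the intention-to-treat set for both co-primaries, with outcomes collected to one month.
3. Allow their removal only from the per-protocol analysis, and report the number operated on, and their events, by arm.

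This changes the analysis set only. How these infants are treated after surgery stays as the protocol already has it.

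The cost is a sentence or two in the eligibility section and continued follow-up of what are probably few infants. The sample size is unchanged. The downside is that some antibiotic courses given for unrelated surgery will enter the duration data; the per-protocol analysis shows whether they matter.

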### Statistical analyses

This trial is designed to exclude a difference in the rates of re-infection or death greater than 2% (non-inferiority aspect of the trial). Assuming a 2% reinfection/death rate in each group, 770 patients are required per arm for a power of 80% at one-sided alpha of 0.025. Based on our data of the study in Lucerne [47], with this number of patients a difference between mean antibiotic therapy durations of 10 hours can be detected at two-sided alpha of 0.05 with a power of 95% (superiority aspect of the trial). To allow for some unevaluable cases 800 per group will be included.

Primary analyses: The two-sided 95% confidence interval for the difference (experimental - control) in re-infection/death rates will be calculated for the total randomized arms and if this difference excludes +2%, non-inferiority is considered to be shown [48]. Comparison of durations of antibiotic therapy will be done using the Mann-Whitney test with stratification by centre. Any patients dying will be considered as the worst outcome in this evaluation and their duration will be set at the highest duration found. All analyses will be done according to the intention-to-treat principle and will be done with stratification by centre. A per-protocol analysis, excluding patients with major protocol violations, will also be done.

Secondary analysis: Exploratory analysis of primary endpoints regarding the relations with and clinical outcomes assessed at T = 24-72 h will be done using logistic regression or Anova. In the Anova the duration's antibiotic treatment will be transformed logarithmically. All tests are two-sided and p = 0.05 is the limit of significance. These analyses will be informal only because it cannot be excluded that the ratings of clinical outcomes at T = 24-72 h are influenced by the PCT results in the PCT-group. In a secondary analysis reinfection/deaths rates will be compared between treatment arms using random effects logistic regression allowing for centre as a random factor.

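### The 770 per arm is correctly computed, but at a 2% event rate no interval tested gives both the stated 80% power and one-sided alpha of 0.025 for non-inferiority.

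*Protocol article*

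**What the plan says.** The Statistical analyses section of the protocol article fixes every input to the non-inferiority calculation.

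- Margin: "This trial is designed to exclude a difference in the rates of re-infection or death greater than 2" percentage points.
- Event rate: "Assuming a 2% reinfection/death rate in each group".
- Size, power and alpha: "770 patients are required per arm for a power of 80% at one-sided alpha of 0.025".
- Allowance for losses: "To allow for some unevaluable cases 800 per group will be included".
- Analysis: "The two-sided 95% confidence interval for the difference (experimental - control) in re-infection/death rates will be calculated for the total randomized arms".
- Decision rule: "if this difference excludes +2%, non-inferiority is considered to be shown".

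The type of interval is not named; a methods reference is cited instead. The same section says that analyses will be stratified by centre. For 800 infants per arm, the Methods/Design part of the abstract says that the power for superiority and for non-inferiority, the latter described as "excluding a disadvantage difference larger than 2% for the experimental arm, will both be greater than 80" per cent.

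**The concern.** A 2% rate in 770 infants is 15.4 expected events per arm. The unpooled normal formula uses the variance at 2% versus 2% for both the alpha term and the power term. Alpha, however, is a property of the rule at the margin, where the experimental rate is 2 points above control and the variance is larger. With few events the Wald interval has a further weakness: when the experimental count happens to be low, its estimated standard error is low too, so the upper limit falls below +2% too often.

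This interval alone decides the safety co-primary (recurrent infection or death). If it is a Wald interval, the chance of declaring non-inferiority for a strategy that truly carries the full 2-point excess is above the stated 2.5%. If it is an interval that holds 2.5%, the stated power is not reached.

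**Working it through.** **Inputs** (Statistical analyses): rate 2% in both arms, margin 0.02, one-sided alpha 0.025, power 80%, 770 evaluable and 800 enrolled per arm.

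**Step 1: reproduce 770.** Unpooled formula:

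n = (1.96 + 0.8416)² × 2 × 0.02 × 0.98 / 0.02² = 7.849 × 0.0392 / 0.0004 = 769.2, rounded up to 770.

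The plan's figure is reproduced.

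**Step 2: the same calculation with the variance at the margin.** When both true rates are 2%, the rates restricted to a 2-point difference are about 3.41% (experimental) and 1.41% (control). The variance sum for the alpha term becomes 0.0341 × 0.9659 + 0.0141 × 0.9859 = 0.0468, against 0.0392 in Step 1. The Farrington-Manning formula then gives

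n = (1.96 × √0.0468 + 0.8416 × √0.0392)² / 0.0004, about 872 per arm.

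**Step 3: exact behaviour of the decision rule.** All pairs of event counts from two independent binomials were enumerated. Non-inferiority is declared when the upper limit of the two-sided 95% interval is below +2%. Power is taken at 2% versus 2%, and one-sided error at control 2%, experimental 4%.

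| Interval | Power, 770 | Error, 770 | Power, 800 | Error, 800 |
|---|---|---|---|---|
| Wald | 79.98% | 2.99% | 81.7% | 2.96% |
| Agresti-Caffo | 78.4% | 2.71% | 80.2% | 2.70% |
| Likelihood ratio | 78.2% | 2.60% | 79.4% | 2.63% |
| Newcombe | 76.8% | 2.46% | 78.5% | 2.45% |
| Score (Miettinen-Nurminen / Farrington-Manning) | 75.6% | 2.35% | 77.1% | 2.31% |
| Wald, continuity-corrected | 74.8% | 2.02% | 76.7% | 2.02% |

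No row has both power of at least 80% and error of at most 2.5%, at 770 or at 800. At 800, the two intervals that pass 80% (Wald and Agresti-Caffo) both exceed 2.5%. A simulation of the Wald rule at 770 gave an error of 3.0%, in agreement.

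**Step 4: could a better-tuned cutoff rescue the pair?** With the cutoff of the Wald, Agresti-Caffo, score or likelihood-ratio statistic adjusted so that the error is 2.5% at the single point 2% versus 4%, the best power at 770 is 78.2%.

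**Step 5: where 80% is reached with alpha held.** On a grid in steps of 10 per arm, exact power for both the score and the Newcombe interval is 80.6% at 850 and stays above 80% from there up to 910, the end of the grid.

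**The case against.** The strongest reply is that nothing is miscalculated. The 770 follows from the stated inputs by a standard formula, sample sizes are conventionally given at nominal alpha, and under the matching Wald interval the article's power figures hold (79.98% at 770, 81.7% at 800). All of this stands. A reader might infer an arithmetic error from the gap; the documents do not support that.

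A second reply is that an article may leave the interval type to the cited reference, the full protocol or the SAP. That also stands, and the unnamed interval is not the complaint. But the choice settles only which stated figure fails. None of the six methods tested delivers the pair, so the later choice does not rescue the claim.

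Third, the shortfall is small beside the uncertainty in the assumed rate. The Discussion reports that antibiotics were restarted in two of 121 neonates in the earlier study, with no deaths, which leaves the rate imprecise. At 770 with a score interval, power would be 85.3% at a true rate of 1.5% and 94.2% at 1%. This is a fair reason to treat the point as modest and not to conclude that the trial is too small. It does not make the stated pair right at the rate the plan itself assumes.

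Fourth, larger Wald errors can be produced: at 770, about 3.2% at a control rate of 1%, 3.8% at 0.5% and 4.5% at 0.2%. A reader might take the upper figures as the size of the problem. They require control rates four to ten times below the assumed 2%, so the figure at the design point is 3.0%.

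Finally, the planned analysis is stratified by centre and the enumeration is not. That is a real limit on the precision of these figures.

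**Conclusion.** The stated pair of 80% power and one-sided alpha of 0.025 at 770 per arm is not achieved. The cause is a normal approximation that is inadequate at about 15 events per arm. At the design rate the choice is between two outcomes:

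- a Wald interval with the stated power and an error of about 3.0%, roughly 0.5 points too high; or
- a score or Newcombe interval that holds 2.5%, with power of about 76-77% at 770 and 77-79% at 800, which is 1.5 to 4.4 points below 80%.

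Among the intervals tested, the abstract's claim of more than 80% at 800 holds only with one that exceeds the stated alpha. The 30 extra infants per arm do not close the gap, and the plan assigns them to unevaluable cases in any event.

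This rests on the plan's own 2% rate, independent binomial counts, equal arms and no centre stratification. The point is a modest correction of a stated operating characteristic. It does not show that the trial is invalid or that more infants must be enrolled.

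**What to change.** Specify a score-type interval for the non-inferiority decision: Miettinen-Nurminen stratified by centre, or Newcombe. Fix it before any comparative data are seen, so that a borderline result cannot turn on the choice. In Statistical analyses and in the abstract, restate non-inferiority power as approximately 76-77% at 770 evaluable and 77-79% at 800 per arm, and say that these figures come from an unstratified calculation.

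Enrolment stays at 800 per arm. The cost is one sentence on the method and a slightly less favourable power figure.
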